##### Exclusion criteria

Participants undergoing therapy (i.e., medication and/or psychotherapy), or presenting substance abuse problems, psychotic symptoms, organic brain disorders (e.g., dementia), self-injury or harming others, or serious health issues that would prevent from using the app, as well as participants reporting scores greater than 1 to question 9 (suicidal ideation) on the PHQ-9 [34] are excluded.

### Study conditions

#### The mHealth intervention

The mHealth CBT intervention comprises the following components: four online intervention modules with specific courses and exercises, activated gradually, a specific assignment for each module, regular automatic messages and assessments, and a therapist check-in per each module.
*Courses* represent the psychoeducational and therapeutic background of the intervention, and include the following topics: information on depression, psychological vulnerability, what CBT is, healthy and unhealthy negative emotions, how behaviors contribute to depression, psychological vulnerability, rational and irrational thoughts, treatment adherence, suicidal thoughts, sleep hygiene, social support, relaxation techniques, and relapse prevention
*Exercises* use the information presented in the courses and follow the structure of a regular therapy session and/or therapeutic homework

The following exercises are included in the app:The *Emotional Pulse* exercise registers the user’s current activity and emotions (healthy or unhealthy)The BA exercises – “My Goals” and “My Activities,” consisting of setting goals and building a list of rewards/pleasant activities to be used in the pursuit of these goalsThe *Find Irrational Thoughts* exercise helps in identifying thoughts behind the emotions found with the Emotional Pulse exercise, andThe *Change Irrational Thoughts* exercise challenges negative/irrational thinking behind unhealthy emotions and replaces it with healthy, flexible, and functional thoughts

Module 1 of the intervention presents information on depression, introduces the user to the CBT approach, and discusses healthy and unhealthy emotions and behaviors. It also introduces the Emotional Pulse and My Goals exercises. Information on suicidal thoughts and treatment adherence is also available.

Module 2 presents information on psychological vulnerability and rational and irrational beliefs, while introducing the Find Irrational Thoughts and Change Irrational Thoughts exercises.

Module 3 presents information on relaxation techniques, also providing video support, along with information on sleep hygiene and social support.

Module 4 focuses on relapse prevention and continued practice of all the exercises.

Participants are informed that they should complete one module every 10 days, within 6 weeks.

### Therapist check-in

Three clinical psychologists provide all clinical contact with the active and placebo intervention participants, via phone calls. Every call is audiorecorded with the participant’s consent. The total therapist time spent per participant is also recorded. The therapists are instructed to limit contact time to approximately 5 min per participant, unless more time is clinically indicated. The therapist check-in component has the role of monitoring app use and mood status, without engaging in therapy, but encouraging intervention adherence.

#### The placebo control group

The active placebo intervention will be delivered via the same platform and largely in the same format as the tested app: it will include largely the same sections and features as the original app (i.e., profile, courses, exercises, evaluation, and messages). The psychoeducation section, although mirroring the structure of the corresponding section in the original app, will include different content, elaborating on common sense strategies of overcoming depression (like positive thinking, listening to music, etc.) and general knowledge about mental and physical health-relevant topics. A Sticky Notes tab will be available in the exercises section, giving the user the possibility of adding content, while suggesting two possible topics: favorite quotes, and a reading journal.

#### The wait-list control group

Participants in the delayed-intervention group are placed on a wait-list for 6 weeks; then they are given full access to the application.

### Outcomes and measures

#### Primary outcomes

The level of depressive symptomatology constitutes the primary outcome.

#### Secondary outcomes

General positive and negative affect and satisfaction with life constitute the secondary outcomes which have been included to assess the efficacy of the application beyond its impact on specific clinical symptoms, e.g., as a possible tool for the improvement of life quality and general wellbeing.

#### Other outcomes

Dysfunctional cognitions, irrational beliefs, and negative automatic thoughts (conceptualized as mechanisms of change) and BA and/or avoidance will be considered as possible predictors of the outcomes. Satisfaction with the application and data regarding the app usage are also assessed.

The instruments used for each of the abovementioned outcomes are presented below:

#### Screening measures

The PHQ-9 [34] is a nine-question instrument designed to correspond to the *Diagnostic and Statistical Manual of Mental Disorder, Fourth Edition, Revised Text* (DSM-IV-TR) [35] diagnostic criteria for major depressive disorder. Respondents rate the items from 0 to 3 according to the frequency of their experience over the previous 2-week period (0 – not at all; 3 – nearly every day). The score can then be interpreted as indicating depression severity (no depression, mild, moderate, moderately severe, or severe depression).

#### Measures of primary, secondary, and other outcomes

The following measures have been adapted into Romanian and successfully used in two previous trials testing another version of the app, and they have shown adequate psychometric properties [36].

The level of depressive symptomatology is assessed with the Center for Epidemiologic Studies Depression Scale–Revised (CESD-R) [37, 38]. The CESD-R is a 20-item self-report instrument, which measures symptoms of depression in nine different groups: sadness (dysphoria), loss of interest (anhedonia), appetite, sleep, thinking/concentration, guilt (worthlessness), tiredness (fatigue), movement (agitation), and suicidal ideation. Participants rate each item on a 5-point Likert scale, from 0 (not at all or less than 1 day) to 4 (nearly every day for 2 weeks) to indicate how they felt or behaved during the last week or so. The total CESD-R score is calculated as a sum of responses to all 20 questions. The CESD-R exhibited good psychometric properties, including high internal consistency, strong factor loadings, and theoretically consistent convergent and divergent validity with anxiety, schizotypy, and positive and negative affect [39].

*The Positive and Negative Affect Scale* (PANAS) [40] is a 20-item self-report questionnaire designed to assess mood. It consists of 10 items that address positive affect (PA) and 10 items that address negative affect (NA). Participants rate each item on a 5-point Likert scale, from 1 (very slightly/not at all) to 5 (extremely) to indicate how they felt during the indicated time frame. The PANAS can be used to assess mood on various time scales by altering the instructions. For the purposes of this study we have used a 2-week time frame. The validity and internal consistency of the PANAS are good, with test-retest reliability being the highest for the “general” temporal instruction. The PANAS has been used previously on the Romanian population and was found to have adequate psychometric properties [41, 42].

*Satisfaction with Life* (SWL) [43] is a five-item scale designed to measure global cognitive judgments of one’s life satisfaction. Participants rate each of the five items using a 7-point scale that ranges from 7 (strongly agree) to 1 (strongly disagree). The SWL has been shown to be a valid and reliable measure of life satisfaction which can be used with a wide range of age groups [44, 45].

*The Dysfunctional Attitudes Scale* (DAS) [46] was designed to measure the intensity of dysfunctional attitudes, which, according to the cognitive theory of depression [47], contribute to vulnerability for depression. For the purposes of our study, we used the short form of this scale. The Dysfunctional Attitudes Scale–Short Form (DAS-SF) [48] consists of two subscales: “dependency” (6 items) and “perfectionism/performance evaluation” (11 items). The 17 items are rated on a 7-point Likert scale, from 1 (total disagreement) to 7 (total agreement). The DAS-SF possesses good psychometric properties in terms of model fit, reliability and convergent construct validity [48].

*The Beliefs Scale* (BS) [49] measures irrational beliefs. It consists of 20 items and responders indicate how much they agree or disagree with each item using a 5-point Likert scale that ranges from 1 (strongly disagree) to 5 (strongly agree). The BS shows good psychometric properties regarding construct and discriminant validity [50].

*The Automatic Thoughts Questionnaire* (ATQ) [51] is a 15-item self-report measure used to assess depression-related cognitions. Participants rate, on a 5-point Likert scale from 1 (never) to 5 (almost all the time), how frequently they have had a given thought over the past week. A higher score shows a higher frequency of automatic thoughts. The psychometric properties of the ATQ have been adequately demonstrated in previous studies [52]. The ATQ has been successfully used previously on the Romanian population [53–55].

*The Behavioral Activation for Depression Scale–Short Form* (BADS-SF) [56] is an instrument designed to be administered weekly to measure changes in avoidance and activation over the course of the BA treatment for depression. The BADS consists of nine items grouped into two subscales (Activation and Avoidance/Rumination). Respondents rate each item on a 7-point Likert scale ranging from 0 (not at all) to 6 (completely). The scale enjoys good psychometric properties [57].

*The Satisfaction with the Application Scale* was specifically designed for this study. It consists of 10 items that assess users’ satisfaction with the application, its difficulty level, attractiveness, and subjective utility. The first eight items are rated on a 3-point scale, ranging from 0 to 2. Each response scale is personalized to the content of the item (e.g., How attractive did you find the exercises included in the application?: 0 = rather unattractive, 1 = attractive enough, 2 = very attractive). Item 9 assesses the application globally, with the participant being asked to give an overall grade between 1 (minimum) and 10 (maximum). Item 10 asks the participants if they would recommend the application to a friend (“yes” or “no” answer).

*The Application Use Scale* was also developed specifically for this study. It consists of eight items that assess weekly quantitative app usage aspects: the effort invested in homework (one item), number of practiced exercises (one item), number of read courses (one item), frequency of general application use (one item), and frequency of every exercise use (four items).

#### Participant timeline

Potential participants will be assessed for eligibility through an initial assessment of depressive symptoms. The initial assessment phase consists of administration of the PHQ-9 and a short phone screening interview. Applicants who do not meet the inclusion criteria are informed via e-mail. They are given a summary score and interpretation for their PHQ-9 score and they are encouraged to discuss their problems with a professional, if necessary. Information on how to reach one – a clinical psychologist or a psychotherapist – is also provided.

After the initial assessment, the participants meeting the inclusion criteria will be randomly assigned to one of the three conditions: (1) active intervention condition – mHealth CBT (group 1), (2) the PI (group 2), or (3) the delayed-intervention condition (WL) (group 3) (see flow diagram in Fig. 4). Subsequent assessments consist of all the instruments presented in the “Outcome measures” section. Figure 5 shows the schedule of enrollment, interventions, and assessments which accords with the SPIRIT figure.

**Fig. 4 Fig4:**
[figure not shown]
Consolidated Standards of Reporting Trials (CONSORT) flow diagram [25] showing subject allocation to the study conditions

**Fig. 5 Fig5:**
[figure not shown]
Schedule of enrolment, interventions, and assessments

The participants in the active intervention and active placebo conditions are assessed at preintervention (time 1 – baseline), at mid-intervention (time 2 – 3 weeks after baseline), at post intervention (time 3 – 6 weeks after baseline), and at 3 months post intervention (time 4). The participants in the delayed-intervention condition are assessed before the waiting period (time 1 – baseline), at mid-waiting period (time 2 – 3 weeks after baseline), and at post waiting period (time 3 – 6 weeks after baseline).

Participants assigned to the active intervention condition will be given access to the online application along with explicit instructions regarding the use of all its sections. Participants will be given 6 weeks to complete the intervention, during which time weekly messages will be sent out to them. Messages include regular assignments designed for a complete and thorough use of the application’s courses and exercises, and encourage the review of materials whenever possible. However, participants are free to use the application at their own pace.

Similarly, the participants in the active placebo condition will be given access to a sham version of the app. During the 6-week intervention period they will be exposed to the same amount of online (i.e., in-app messages) and therapist communication as the active intervention participants.

After each week, participants’ app use is evaluated (see the Application Use Scale described above). Similarly, after each week of using the app, the participants are required to complete the CESD-R to monitor their depressive symptomatology and provide individualized in-app feedback on their emotional state.

The participants in the delayed-intervention condition are placed on a wait-list for 6 weeks, after which time they are given full access to the app.

#### Sample size

A total of 165 participants with moderate depressive symptomatology was estimated. This is based on previous studies on the efficacy of mobile phone applications for depression, which reported small to moderate between-group effect sizes [19, 24]. An a priori sample size calculation was conducted with G*Power 3.1.9.2 [58, 59] for analysis of variance (ANOVA) (repeated measures, between factors), assuming an alpha level of 0.05, a statistical power of 0.80, and a small to medium effect size (*f* = 0.2). Since the current protocol has a therapist check-in component, a sample size recruitment target of *N* = 220 was set to allow for sample attrition, thus estimating a dropout rate of approximately 30%.

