**Methods/design:**

Romanian-speaking adults (18 years and older) with access to a computer and the Internet and owning a smartphone are included in the study. A randomized, three-arm clinical trial is being conducted (i.e., active intervention, placebo intervention and delayed intervention). Two hundred and twenty participants with moderate depressive symptoms (i.e., obtaining scores >9 and ≤16 on the Patient Health Questionnaire, PHQ-9) will be randomized to the three conditions. Participants undergoing therapy, presenting serious mental health problems, or legal or health issues that would prevent them from using the app, as well as participants reporting suicidal ideation are excluded. Participants randomized to the active and placebo interventions will use the smartphone app for 6 weeks. A short therapist check-in via phone will take place every week. Participants in the delayed-intervention condition will be given access to the app after 6 weeks from randomization. The primary outcome is the level of depressive symptomatology. The intervention delivered through the app to the active condition includes psychoeducational materials and exercises based on CBT for depression, while the placebo intervention uses a sham version of the app (i.e., similar structure of courses and exercises).

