### Assignment to study group

The participants are randomly assigned to one of the three trial arms, using the software Randomizer.org. Randomization is performed by a research assistant using a simple (unrestricted) randomization sequence that assigns three unique numbers per participant; the number assigned is either 1, 2, or 3 according to the number of the experimental condition. To conceal the allocation mechanism, the same research assistant will monitor the assessments and allow access to the application for the participants in the wait-list control group after 6 weeks. The principal investigator and the statisticians running the data analysis will remain blinded to the study condition until the completion of the study.

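### A recruitment target of 220 covers 25% dropout, not the stated 30%; at 30% about 154 participants complete, 11 short of the required 165

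*Protocol article*

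**What the plan says.** The Sample size section of the protocol article gives the requirement first: "A total of 165 participants with moderate depressive symptomatology was estimated". The calculation was done in G*Power for "analysis of variance (ANOVA) (repeated measures, between factors"; its inputs are given as "assuming an alpha level of 0.05", "a statistical power of 0.80" and "a small to medium effect size (*f* = 0.2".

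The section then sets a recruitment target of 220, which "was set to allow for sample attrition, thus estimating a dropout rate of approximately 30" per cent.

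The Methods/design part of the abstract confirms that 220 is the number to be randomised: "Two hundred and twenty participants with moderate depressive symptoms" are to be allocated to the three conditions. No other section gives a different base sample size or dropout rate.

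**The concern.** The purpose of the 220 is to leave 165 participants after attrition. Because 220 is the number randomised, a dropout rate has to be counted from 220, and 220 less 30% is not 165.

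A reader of the Sample size section would conclude that the trial keeps 80% power through a 30% loss, and on the section's own numbers it does not. Attrition matters in this setting: the Background notes that high attrition limited the benefit of computerised CBT, and the Data collection methods section gives a paragraph to retention. The allowance for dropout should therefore be a figure that the trial can rely on.

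**Working it through.** **Inputs.** From the Sample size section: required N = 165, alpha 0.05, power 0.80, f = 0.2, target 220, dropout about 30%. From Assignment to study group: "The participants are randomly assigned to one of the three trial arms", so k = 3 groups, taken as equal in size. The number of measurements m and their correlation ρ are not stated for the calculation, so they are assumptions below.

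**Step 1: reproduce the 165.** For the between-groups test in a repeated-measures ANOVA, the noncentrality parameter is λ = f² × N × m / (1 + (m − 1)ρ), with k − 1 and N − k degrees of freedom.

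- With m = 3 and ρ = 0.5 at N = 165: λ = 0.04 × 165 × 3 / 2 = 9.9, power 0.804. The smallest N in multiples of three that reaches 0.80 is 165.
- With m = 4 and ρ = 0.55 at N = 165: λ = 0.04 × 165 × 4 / 2.65 = 9.96, power 0.806. The smallest N is again 165.

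The base figure therefore reproduces, though not from a unique setting.

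**Step 2: the dropout that 220 covers.**

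- Retained fraction: 165/220 = 0.75, so the dropout covered is 25.0%.
- Check: 165/(1 − 0.25) = 220 exactly.

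**Step 3: what 30% dropout implies.**

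- Completers from 220: 220 × 0.70 = 154, which is 165 − 154 = 11 short.
- Target needed: 165/(1 − 0.30) = 235.7, so 236, which is 236 − 220 = 16 more than planned.
- Per arm, if equal: 165/3 = 55 against 154/3 ≈ 51.

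**Step 4: possible origin.** The allowance is 220 − 165 = 55. Taken on the required sample it is 55/165 = 33%, and 165 × 1.30 = 214.5, or 215, is not far from 220. The percentage may therefore have been taken on the evaluable sample instead of the enrolled one. This is an inference, and the contradiction does not depend on it.

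**Step 5: power at 154, if dropouts contribute no data.**

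| Assumed m, ρ | Required N | Power at 165 | Power at 154 |
|---|---|---|---|
| 3, 0.5 | 165 | 0.804 | 0.774 |
| 4, 0.55 | 165 | 0.806 | 0.776 |
| 4, 0.5 | 156 | 0.830 | 0.801 |

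The first two rows reproduce the published 165 and put power at about 77%. The third stays just above 80% at 154, but it would have required 156, so it cannot be the setting behind the published figure. In all three rows the loss is about 3 percentage points.

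**The case against.** Four points can be made on the other side.

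1. **Dropouts are not lost to the analysis.** The Statistical methods section plans an intention-to-treat analysis with data carried forward and a mixed-effects model, both of which keep participants with partial data. All arms have a mid-period assessment, and app users complete the CESD-R weekly. Many of the 66 expected dropouts (220 − 154) would contribute something. This stands: 154 is not the analysed sample, and 77% is a completers-only, worst-case figure. Partial data do not restore full information, however, so some loss of power remains.
2. **The G*Power setting is not fully stated.** This also stands. The values of m and ρ are assumptions, not the sponsor's published inputs. The two settings shown that reproduce 165 nevertheless agree to within half a percentage point.
3. **The text says approximately, and the effect is small.** The effect is small: about 3 points of power and about 4 participants per arm, and simple unrestricted randomisation can move arm sizes by more than that. But the hedge does not cover the gap. The target equals 165/0.75 exactly, and a target built on 30% would lie near 236.
4. **No design decision changes.** The endpoint, the analysis and the recruitment target can all stay as they are. That makes the correction easy to carry out; it does not make the stated dropout allowance right.

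**Conclusion.** The point holds. The required sample, the recruitment target and the dropout rate in the Sample size section are mutually inconsistent: 220 covers 25% dropout, 30% leaves 154, and 30% would need 236. These results use only figures printed in the article.

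The consequence is modest. Power in the stated calculation would be about 77% instead of 80% at 30% dropout. That figure assumes equal arms, values of m and ρ chosen to reproduce 165, and dropouts who contribute no data; the true loss should be smaller to the extent that partial data are used. The 77% refers to the three-group omnibus test, not to the comparison of app with placebo alone. The text should be corrected, but the design is not in question.

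**What to change.** Reword the attrition sentence in the Sample size section in one of two ways.

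- If 220 was meant to secure 165 completers, state that the target allows for 25% dropout.
- If 30% is the real expectation, keep 220 and state that about 154 participants are expected to complete. Add that power in the stated calculation is then about 77% if dropouts contribute no data, and give the number of measurements and the correlation used.

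Either version costs one sentence and no additional participants. Keeping both the 30% and the 165 would instead mean raising the target to 236, here and in the abstract, at a cost of 16 more participants.
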